**Fig. 4 Fig4:**
[figure not shown]
Intervention

Women will be encouraged/sensitised to continue with their scheduled ANC visits to receive other essential ANC services in addition to IPTp-SP doses in between the annual SMC cycles.

Control arm

Women will receive monthly IPTp-SP doses through scheduled ANC visits (standard care) only.

### Sample size calculation

#### Primary endpoint – IPTp3 + at endline

The primary endpoint will be collected at endline among women with a child less than 12 months.. It will be the individual level binary indicator for presence or absence of at least three doses of IPTp-SP through ANC alone or ANC plus SMC delivery platforms. Since baseline prevalence of IPTp-SP coverage highly differs between Mali and Burkina Faso, the sample size was calculated for each country separately.

In Mali, with 10 clusters per arm, 48 women sampled per cluster will be required at endline to detect a 45% increase in the relative risk of women receiving at least 3 doses of IPTp-SP between control and intervention arms, with 80% power, alpha = 5%, an intra-cluster correlation coefficient (ICC) of 2.5% and 5% primary endpoint missing rate, assuming this proportion to be 28% in the control arm [20]. Based on this assumption a total of 1,008 women will be included (Shiny CRT calculator®) [21]. With this sample size, we should be able to demonstrate a 33% in the relative risk of women receiving at least 3 doses of IPTp-SP assuming this proportion to be 40% in the control arm as recently reported in an HHS conducted in a neighboring area, Bankass in Mopti region ([name] et al., 2022, unpublished data). Assuming that there will be at least one eligible woman in every 5 households, a total of 5,040 households will be visited.

In Burkina Faso, with 10 clusters per arm, 46 women sampled per cluster will be required at endline to detect an increase of 22% in the relative risk of women with at least 3 doses of IPTp-SP between the control and intervention arms, with 80% power, alpha = 5%, an ICC of 2.5% and 5% primary endpoint missing rate, assuming this proportion to be 58% in the control arm [18]. Based on this assumption a total of 966 women will be included. Assuming that there will be at least one eligible woman in every 5 households, a total of 4,830 households will be visited.

A possible adjustment of the number of women to be interviewed in the endline surveys will be made based on the baseline data: IPT3 + coverage; proportion of non-response and calculated ICC.

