### Study site

The study is conducted in two Sahelian countries with highly seasonal malaria transmission where SMC has been implemented since 2012 (Fig. 3). In Burkina Faso, the study site is Boussé District located at 55 kms North-East from Ouagadougou. The population in 2019 was estimated at 189,937 inhabitants [16]. In 2020, the coverage of IPTp3 + and SMC was 55.9% and 103%, respectively [17]. In Mali, the study site is the district of Kangaba located at 85 kms South-West of Bamako with an estimated population of 146,563 inhabitants in 2021. The district belongs to the region of Koulikoro which has 33.8% coverage of IPTp3 + [18] and that of SMC at > 100% in the district [19].

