### Analysis plan

#### Primary endpoints—SMC, IPTp-SP, and ANC analysis

The primary outcome will be the individual level binary indicator for presence or absence of at least three doses of IPTp-SP in women included in the endline IPTp-SP HHS, and the intervention effect will be estimated using a generalized linear mixed model with a logit link function and a random intercept term for cluster – period, expressed as odds ratio and 95% confidence intervals. The primary analysis will be done by country. In a secondary analysis, data of both countries will be combined using an individual patient data meta-analysis approach to assess the overall efficacy of the intervention.

Evolution over time, and by arm, of the use of ANC (number and timing of contacts) will be assessed using routine data and modelling-temporal analysis. In addition, a multilevel logistic regression model will be performed to identify individual and contextual factors associated with ANC attendance and IPTp-SP coverage at baseline. Multilevel modelling will be selected due to the clustering of the collected data.

Differences in SMC coverage (3 or 4 doses) and ANC uptake (4 visits) between control and intervention arms at endline will be assessed using multilevel regression models.

No interim analysis will be conducted.

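### The stated 80% power in each country holds only with normal critical values; with 10 clusters per arm, a test that keeps the 5% level has about 75% to 76%

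*Protocol article*

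**What the plan says.** The Protocol article, under Sample size calculation (Primary endpoint – IPTp3 + at endline), does a separate calculation for each country. For Mali: "In Mali, with 10 clusters per arm, 48 women sampled per cluster will be required at endline". The effect assumed there is a relative risk of 1.45 on a control proportion of 28%, "with 80% power, alpha = 5%, an intra-cluster correlation coefficient (ICC) of 2.5% and 5% primary endpoint missing rate". The same numbers are said to cover a 33% relative increase from 40%. For Burkina Faso: "In Burkina Faso, with 10 clusters per arm, 46 women sampled per cluster will be required at endline". The effect assumed there is a relative risk of 1.22, "with 80% power, alpha = 5%, an ICC of 2.5% and 5% primary endpoint missing rate, assuming this proportion to be 58% in the control arm". The totals are 1,008 and 966 women. No t-distribution or allowance for the small number of clusters is mentioned.

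The Analysis plan (Primary endpoints—SMC, IPTp-SP, and ANC analysis) makes the by-country analysis primary and the combined analysis secondary. The model is a "generalized linear mixed model with a logit link function and a random intercept term for cluster" and period, reported as an odds ratio with a 95% confidence interval. Neither the estimation method nor the reference distribution is named.

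The sample size section ends with a provision: "A possible adjustment of the number of women to be interviewed in the endline surveys will be made based on the baseline data". Its inputs are coverage, non-response and the calculated ICC.

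**The concern.** In a cluster-randomised comparison, the precision of the arm contrast depends on a between-cluster variance that must itself be estimated. With 10 clusters per arm, that estimate has 18 degrees of freedom, and the two-sided 5% critical value is 2.101, not 1.960. A calculation that uses 1.960 overstates the power of any test that holds its level.

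Both primary comparisons are affected, because the 40 clusters are pooled only in a secondary analysis. The Abstract and the Discussion repeat the claim that the trial is powered for increases of 45% and 22%. The planned adjustment after baseline would carry the same optimism forward if it reused the normal formula.

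**Working it through.** **Inputs (Sample size calculation, Primary endpoint).** k = 10 clusters per arm; m = 48 (Mali) or 46 (Burkina Faso); ICC = 0.025; alpha = 5%, taken as two-sided (sidedness is not stated, but two-sided reproduces the figures). Proportions: Mali 0.28 to 0.28 × 1.45 = 0.406; Mali alternative 0.40 to 0.40 × 1.33 = 0.532; Burkina Faso 0.58 to 0.58 × 1.22 = 0.7076.

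**Women analysed.** 48 × 20 × 1.05 = 1,008 and 46 × 20 × 1.05 = 966. After 5% missing, 1,008 × 0.95 / 20 = 47.9 and 966 × 0.95 / 20 = 45.9 per cluster. The missing-data allowance therefore leaves 48 and 46 analysed and gives no spare power.

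**Formulas.** DE = 1 + (m − 1) × 0.025. SE = √[(p0q0 + p1q1) × DE / (km)]. λ = (p1 − p0) / SE. Normal power = Φ(λ − 1.960). t power = probability that a non-central t with 18 df and non-centrality λ exceeds 2.101.

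| Scenario | DE | p0q0 + p1q1 | SE | λ | Normal power | t(18) power |
|---|---|---|---|---|---|---|
| Mali, 28% | 2.175 | 0.2016 + 0.2412 | 0.0448 | 0.126/0.0448 = 2.813 | 80.3% | 75.8% |
| Mali, 40% | 2.175 | 0.2400 + 0.2490 | 0.0471 | 0.132/0.0471 = 2.804 | 80.1% | 75.6% |
| Burkina Faso, 58% | 2.125 | 0.2436 + 0.2069 | 0.0456 | 0.1276/0.0456 = 2.797 | 79.9% | 75.3% |

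The normal column reproduces the plan's 80% in all three scenarios. With a pooled variance the normal figures are 79.8%, 79.6% and 79.4%, and the t figures 75.3%, 75.0% and 74.8%.

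**Cluster size solved for 80%.** The normal formula gives 47.1 (Mali 28%), 47.8 (Mali 40%) and 46.3 (Burkina Faso), which are the plan's 48 and 46. The t formula needs 62, 63 and 61 analysed women per cluster (64, 65 and 63 with pooled variance), or 11 to 12 clusters per arm at the planned cluster size.

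**Detectable effect.** At the planned numbers, 80% power with t(18) corresponds to relative risks of about 1.47, 1.35 and 1.23.

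**Check by simulation.** A cluster-level t-test on beta-binomial clusters (100,000 runs) had type I error 4.9% and 5.0%, and power 75.5% (Mali 28%) and 75.1% (Burkina Faso).

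**The other route, conditional on the method.** A logit mixed model with one intercept per cluster was fitted by maximum likelihood to endline data with logit-normal clusters and tested by Wald z (4,000 null runs, 2,400 alternative runs per country). Type I error was 7.7% (Mali) and 8.3% (Burkina Faso); with beta-binomial clusters it was 8.0% and 8.4%. Apparent power was 82% and 81%, falling to 75% and 73% once the critical value was set to give a true 5%. If the between-cluster variance is estimated without bias but a z reference is kept, type I error is about 6.6%.

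**The case against.** **The article does not say that its intervals are uncorrected.** This stands. It names a mixed model and a 95% interval, but no estimator or degrees-of-freedom method, and an article commonly leaves those to the analysis plan, which is not shown. A reader might infer that the trial will run at 8% type I error. The documents do not support that: the figure belongs to one assumed implementation, with a single intercept per cluster fitted to endline data alone, whereas the stated random term is for cluster and period. The power figure does not depend on this silence: no later choice of method gives 80% power at a true 5% level with the stated inputs.

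**Lost power and inflated error cannot both be charged.** This also stands; they are alternatives. With a correction, the level is about 5% and power 75% to 76%. Without one, apparent power stays slightly above 80% and the level is about 8%.

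**The effect is small beside the other planning uncertainty.** Largely true. The detectable relative risk moves by 0.01 to 0.02, and with an ICC of 0.020 instead of 0.025 the t-based power for Mali is already 80.4% (28%) and 80.2% (40%). This limits the severity but does not make the stated figure right at the stated ICC.

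**The plan can already close the gap.** At the planned ICC this is correct: 61 to 65 analysed women per cluster restore 80%. One might go further and say that adding women cannot help, since above an ICC of about 0.041 no cluster size reaches 80% with t(18). Nothing in the documents points to an ICC that high, so this is a hypothetical limit, not an error in the plan.

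**The Burkina Faso district figure.** The Study site section says "In 2020, the coverage of IPTp3 + and SMC was 55.9% and 103%, respectively", against the 58% used for planning. One might add this to the shortfall, but it concerns an input, not the reference distribution, and baseline coverage is already an input to the planned adjustment.

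**Conclusion.** Wrong as written; moderate severity. The 80% is the result of a normal approximation. A by-country test that holds 5% with 18 degrees of freedom has about 75% to 76% power in all three stated scenarios, a shortfall of 4 to 5 percentage points. This rests on the plan's own ICC of 2.5%, equal cluster sizes of 48 and 46 analysed women, a two-sided 5% level and the stated control proportions. The figure of about 8% type I error is what would follow if no small-sample method were used with a maximum-likelihood fit. It is a reason to name the method, not a finding that the trial will use an invalid one.

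**What to change.** 1. In the sample size section, restate power as about 76% in each country. Alternatively, keep 80% and restate the detectable relative risks as about 1.47 (Mali, 28%), 1.35 (Mali, 40%) and 1.23 (Burkina Faso). Align the Abstract, the primary hypothesis and the Discussion.
2. State that primary inference uses a small-sample method: a cluster-level t-test with 18 degrees of freedom, or the mixed model with a small-sample degrees-of-freedom correction. If the analysis plan already does so, a cross-reference is enough.
3. Run the baseline-driven adjustment of women per cluster with the t-based formula.

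Items 1 and 2 cost a slightly less favourable stated power and need no extra data. More interviews arise only if the sponsor uses item 3 to restore 80%. At the planned ICC, that would mean about 62 × 20 × 1.05 = 1,302 women in Mali for the 28% scenario (294 more than 1,008) and 61 × 20 × 1.05 = 1,281 in Burkina Faso (315 more than 966).

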#### Sample size – IPTp-SP and SMC coverages at baseline

The baseline HHS will determine IPTp-SP coverage among women who have delivered in the previous 12 months, and SMC coverage among children living in the study districts, in the two countries.

Table 1 shows the sample size calculated for the baseline IPTp-SP and the SMC HHS based on the following equation [22]:

**Table 1 Tab1:** Estimated sample size for baseline IPTp-SP and SMC HHS

Country	Outcomes		Estimated sample size	Estimated number of households to be visited^a^
**Mali**	Estimated IPTp3 +	28%, up to 40%	775	3,875
	Estimated SMC coverage 4 doses	54%	802	802
**Burkina Faso**	Estimated IPTp3 +	58%	786	3,930
	Estimated SMC coverage 4 doses	90%	290	290

^a^It is assumed that at least one woman in every five households will meet the inclusion criteria and there will be a non-response rate of 5%. Sources: MIS 2018, for Burkina Faso [18]; ACCESS SMC partnership [23]; Diawara et al. 2017 [24] and [name] et al. 2022, unpublished data, for Mali

$$n=\frac{DE\cdot{1.96}^2\cdot p\cdot\left(1-p\right)}{{precision}^2}$$

Where Design Effect (DE) = 2, *p* = expected IPTp3 + coverage, or the expected SMC coverage, prevalence precision =  ± 0.05 with a 95% CI. It is assumed that at least one woman in every five households, and one child in every household will meet the inclusion criteria and there will be a non-response rate of 5%.

#### Sample size – SMC coverage at endline

The endline SMC HHS will be conducted 16 months after the implementation to determine the coverage of four doses of SMC among 3–59 months old children in project districts in the two countries and test for differences in SMC coverage between control and intervention arms.

For IPTp-SP coverage at endline we expect to visit 5,040 households in Mali, and 4,830 in Burkina Faso, which we expect will be all eligible for the SMC HHS. Among them, 880 and 120 children (one per household) randomly selected in Mali and Burkina Faso respectively will give us 80% power at 5% alpha to detect a relative difference of 25% in SMC between control and intervention arms, assuming prevalence in control arm is 54% (Mali) and 90% (Burkina Faso).

#### Secondary endpoints

Feasibility and acceptability

To assess the acceptability and feasibility of IPTp-SP delivery through the ANC + SMC strategy, a purposive sample of 40 to 80 pregnant women of different gravidities and women with a child < 12 months. per country (80 to 160 total) will be recruited at endline. An additional purposive sample of 48 to 72 women will be selected for Focus Group Discussions (FGDs). Two to four health providers purposively selected from each of the 10 intervention HFs in each country (40 to 80 total) and all consenting CHWs who were involved in the IPTp-SP community delivery will be included. The interviews will also include the DHMTs and Ministry of Health staff in the National Malaria Control and Reproductive Health departments (approx. 5 per site, *n* = 10).Systems effectiveness

ANC exit interviews will be conducted with pregnant women when leaving the HF at endline to assess the systems effectiveness of the IPTp-SP delivery in both arms (intervention and control). In Mali, a sample size of 699 women from 20 HF will allow the detection of an estimated 35% of women achieving the primary endpoint of IPTp3 + with a precision of ± 5%, 95% CI, and a DE of 2. In Burkina Faso, a sample size of 699 women from 20 HF will allow the detection of an estimated 65% of women achieving the primary endpoint of IPTp3 + with a precision of ± 5%, 95% CI, and a DE of 2.Exploratory COVID

To assess women’s ANC and IPTp-SP care seeking practices and any impact that the COVID-19 pandemic had on delivery and access at baseline, a purposive sample of 8–12 pregnant women of different gravidities and women with a child < 12 months. will be selected (80–120 women per country for a total of 160–240) for FGD, and a purposive sample of 2–3 health care providers will be selected from 10 HFs in both countries (20–30 per country for a total of 40–60) for in-depth interviews.

### Data collection

Primary endpoints—Household surveys for IPTp-SP, SMC, and ANC

The tablet-based survey using REDCap will be in French; the surveyors will conduct the survey in the language of the participant’s choice based on the translated questionnaire and submit the responses to the tablet in French. Surveyors will not be members of the villages they survey, nor will they be members of the intervention health care delivery staff. All surveyors will be female, as the survey tool contains potentially sensitive questions (i.e., number of pregnancies, details about a potential stillbirth, miscarriage, etc.). ANC and IPTp-SP cards will be checked for concordance with women’s self-report of ANC visits and IPTp-SP doses.

Data on SMC uptake will be collected by interviewing children’s mothers/guardians and through review of children’s SMC cards one week after the last SMC round.

#### Secondary endpoints

Feasibility and acceptability

In-depth interviews will be conducted at endline among health managers, ANC providers, CHWs, pregnant women and women with a child < 12 months., and key informants (local authorities) in both study arms to explore their perceptions and experiences with the intervention.

FGDs with pregnant women and women with a child < 12 months will be undertaken at baseline to explore women’s ANC and IPTp-SP care seeking practices and any impact that the COVID-19 pandemic had on delivery and access. FGDs with pregnant women and women with a child < 12 months., and husbands or heads of households will be conducted at endline to explore their perceptions on the feasibility and acceptability of the proposed integrated delivery strategy.

All in-depth interviews and FGDs will use topic guides and will be recorded. Audio files will be transcribed in the local language and translated into English with quality checks at each stage of transcription and translation. Transcripts will be imported to NVivo version 12 for coding. Field notes will be typed and imported into the Nvivo project for subsequent analysis.Exploratory COVID

In-depth interviews will be conducted at baseline among ANC providers, CHWs and pregnant women and women with a child < 12 months. to assess pregnant women’s ANC and IPTp-SP care seeking practices and any impact that the COVID-19 pandemic had on delivery and access.Systems effectiveness: ANC exit interview

Pregnant women will be approached as they come into the facility and asked to participate in the study. A structured questionnaire will be used to interview enrolled pregnant women as they exit ANC. Topic categories within the questionnaire will include demographics, current and past pregnancy history, reason for attendance on the day of the interview, IPTp-SP received on the day of the interview by DOT and information given by the health provider, IPTp-SP doses received during previous ANC visits or home visits by CHWs during that pregnancy, and any other medication received. ANC and IPTp-SP cards check will also be performed to assess concordance with women’s self-report.Process evaluation

In parallel with the main trial, we will conduct a mixed-methods process evaluation to assess whether the study intervention was implemented as intended based on the MRC guidance for process evaluation of complex interventions [25]. The process evaluation will assess the following implementation parameters: fidelity; dose; reach; context; and adaptations made to the intervention in the study context(s). Additional complementary qualitative data from interviews with participants and implementers will clarify potential mechanisms through which the intervention achieved outcomes. These insights are of value within the context of the diverse large scale effectiveness trial settings and will inform future scale-up and sustainability.

Figure 5 summarises the pre-study intervention logic model for the evaluation, describing the proposed causal relationships between the intervention components and outcomes. This model represents the study’s initial overarching conceptual framework to structure data collection and analysis and maintain consistency across countries.Clinical outcomes

**Fig. 5 Fig5:**
[figure not shown]
Logic model

Individual data on IPTp-SP coverage and ANC attendance will be collected from ANC cards and registers to triangulate with women’s self-reported data from household surveys. These data will be extracted for all ANC clinic attendees during the study period. All registers will be reviewed and data on gestational age and IPTp-SP administration extracted onto electronic study forms previously designed in REDCap, using tablets.

The number of confirmed malaria cases in both children and pregnant women will be recorded from hospital and health centres in both intervention and control arms in all clusters. From the same clusters, pregnancy outcomes from women who deliver in a health facility will be monitored at delivery to record birth weight, preterm delivery, still birth, miscarriage. Table 2 shows the outcomes and their related objectives, methods and timeline.

**Table 2 Tab2:** Study objectives, outcomes, methods, and timeline

Study objectives	Outcomes	Methods	Timeline
1. To compare the delivery of IPTp-SP through the integrated strategy (ANC + SMC) with standard care (ANC)	The proportion of women who received at least 3 doses of IPTp-SP during pregnancy	• Household survey of women with a child < 12 months	• Baseline • Endline
2. To assess the acceptability and feasibility of ANC + SMC delivery of IPTp-SP compared to standard care (ANC) among health providers, CHWs, and pregnant women and women with a child < 12 months	Major themes emerging through thematic analysis using a theory of acceptability (developed a priori)	• In-depth interviews • Focus group discussions	• Endline
3. To assess the systems effectiveness of the integrated delivery of IPTp-SP	Cumulative systems effectiveness of IPTp-SP delivery at ANC + SMC	• ANC exit interview of ANC attendees	• Endline
4. To assess any increase or decrease in ANC uptake following the integrated ANC + SMC IPTp-SP delivery	The proportion of women with 4 + ANC visits during pregnancy	• Household surveys of women with a child < 12 months • Routine data collection: individual facility data on ANC attendance	• Baseline • Endline • Throughout the trial
5. To assess any increase or decrease in SMC uptake following the integrated ANC + SMC IPTp-SP delivery	The proportion of children 3–59 months who received 4 doses of SMC	• Household surveys of mothers of children 3–59 months	• Baseline • Endline
6. To estimate the number of malaria cases in both children and pregnant women over the course of the trial, by arm	Confirmed malaria • incidence rates and malaria positivity (RDT + /RDT performed) ratios	• Routine data collection: individual facility data on malaria cases for pregnant women and children 3–59 months	• Throughout the trial
7. To estimate the number of poor birth outcomes in women over the course of the trial, by arm	• The proportion of women with miscarriage, stillbirth, low birth weight, or preterm birth	• Routine data collection: individual facility data on birth outcomes	• Throughout the trial
8. To assess care-seeking practices during COVID and the anticipated acceptability of the integrated strategy of ANC + SMC delivery of IPTp-SP	• Major themes emerging through thematic analysis using a theory of acceptability (developed a priori)	• In-depth interviews with healthcare providers • Focus group discussions with women	• Baseline

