## Methods/Designs

### Objectives and hypothesis

The main objective of this study is to evaluate whether the integration of IPTp-SP delivery to SMC in addition to ANC delivery will increase the coverage of IPTp-SP and ANC among pregnant women in Mali and Burkina Faso. The primary hypothesis is that integrated ANC + SMC strategy (intervention) as compared to the ANC (standard of care) will increase coverage defined as an increase in coverage of ‘at least 3 doses’ of IPTp-SP, by 45% in Mali and 22% in Burkina Faso, and support the goal of improving the prevention of malaria in pregnancy and reducing adverse birth outcomes in Sahelian pregnant women.

The primary objectives are: (1) to compare the delivery of IPTp-SP through the integrated strategy with standard of care, (2) to assess the acceptability and feasibility among health providers and pregnant women, (3) to assess the systems effectiveness at implementing the integrated delivery strategy and (4) to estimate the incremental cost-effectiveness of the integrated versus standard of care strategy from the societal perspective. (Economic protocol to be published separately).

The secondary objectives are: (1) to assess any increase or decrease in SMC or ANC uptake following the integrated ANC + SMC IPTp-SP implementation, (2) to estimate the number of malaria cases in both children and pregnant women over the course of the trial, and (3) to assess pregnancy outcomes at delivery (birth weight, miscarriage, stillbirth, preterm birth) in both the intervention and control arms among women delivering at health facilities (HF).

An exploratory objective will assess women’s ANC and IPTp-SP care seeking practices and any impact that the COVID-19 pandemic had on their delivery and access.

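### Miscarriage is listed among outcomes recorded at delivery in women who deliver in a health facility; that rule leaves miscarriages largely unobserved, so a miscarriage figure by arm cannot be interpreted

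*Protocol article*

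**What the plan says.** Three places in the protocol article bear on this outcome.

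- **Objectives and hypothesis, secondary objective 3.** The aim is "to assess pregnancy outcomes at delivery (birth weight, miscarriage, stillbirth, preterm birth", and the population is given as "in both the intervention and control arms among women delivering at health facilities".
- **Data collection, Clinical outcomes paragraph (text beside the logic model).** "pregnancy outcomes from women who deliver in a health facility will be monitored at delivery to record birth weight, preterm delivery, still birth, miscarriage".
- **Row 7 of Table 2.** The outcome is "The proportion of women with miscarriage, stillbirth, low birth weight, or preterm birth", by arm. The source is "Routine data collection: individual facility data on birth outcomes", collected throughout the trial.

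Two other data sources touch on pregnancy loss or early pregnancy, but neither is listed for this objective. The household survey tool asks for "details about a potential stillbirth, miscarriage". The ANC register review covers all ANC attendees and has "data on gestational age and IPTp-SP administration extracted onto electronic study forms".

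**The concern.** Delivery in a facility is the condition for entering the outcome dataset, and delivery is the moment of observation. Miscarriage is an event that ordinarily removes a pregnancy before that moment. The population and time point thus conflict with one of the outcomes they are meant to serve. The restriction appears both in the objectives and in the data collection text, so it is not a single slip of wording.

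The trial would report, by arm, a miscarriage figure whose numerator depends on how many losses happen to be entered in facility records and whose denominator is made up of pregnancies that reached delivery. A low figure in both arms could be taken for an absence of difference. A difference between arms could come from recording rather than from pregnancy loss. If Table 2, row 7 is meant as one combined proportion, the same weakness enters that proportion.

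This is separate from the restriction to facility births, which the article states openly. Even if every birth took place in a facility, the rule would not be designed to observe miscarriages.

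**Working it through.** The article gives no rate, sample size or power for miscarriage or for the combined proportion, so there is no stated figure to reproduce. The check is to follow pregnancies through the rule and then look for another source.

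**1. What the rule does with each kind of pregnancy**

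- Birth in a facility, live or stillborn: in the denominator, with birth weight, prematurity and stillbirth observable.
- Birth outside a facility: in neither numerator nor denominator, by the stated restriction.
- Miscarriage never seen at a facility: in neither.
- Miscarriage managed at a facility: not a delivery on the wording, so in neither. In practice it might still be entered, because Table 2, row 7 refers broadly to individual facility data. The article does not say whether it would be.

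**2. Whether another source fills the gap**

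- Household survey: Table 2 describes it as "Household survey of women with a child < 12 months". The baseline sample-size section speaks of women who delivered in the preceding 12 months. Either way, selection is through a birth, so a pregnancy ending in miscarriage is not what brings a woman into the sample. A loss can be reported as history, but row 7 does not name the survey as a source.
- ANC registers: these cover all attendees, but the items named are ANC attendance, gestational age and IPTp-SP administration, not pregnancy loss.
- ANC exit interviews: these reach women who are currently pregnant. They ask about pregnancy history but are not a source for row 7.

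**3. What the recorded proportion would measure**

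Let *m* be the true miscarriage risk, *c* the share of miscarriages that end up in the facility outcome record, and *f* the share of other pregnancies delivered in a facility. Then

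recorded proportion = *m·c* / (*m·c* + (1 − *m*)·*f*).

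Read literally, *c* = 0 and the recorded proportion is 0 for any *m* and *f*. None of the three inputs is in the article. The following values are assumptions chosen to show the behaviour, with *f* = 70%:

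- *m* = 5%, *c* = 5%: 0.0025 / (0.0025 + 0.665) = 0.4%
- *m* = 10%, *c* = 5%: 0.005 / (0.005 + 0.63) = 0.8%
- *m* = 15%, *c* = 5%: 0.0075 / (0.0075 + 0.595) = 1.2%
- *m* = 10%, *c* = 50%: 0.05 / (0.05 + 0.63) = 7.4%

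With the true risk held at 10%, the recorded figure runs from 0% to 7.4% as *c* moves from 0 to 50%. It is governed by *c*, which the plan neither fixes nor measures. Nothing guarantees that *c* is equal in the two arms: the Background expects the strategy to raise ANC attendance, and contact with the facility may affect whether a loss is recorded.

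**The case against.** The best reply is that the wording is loose rather than wrong. The sentence that speaks of women who deliver also lists miscarriage, so the authors may have meant any pregnancy ending in a facility. Table 2, row 7 names facility data in general, not a delivery register, and the full protocol may define the sources. The outcome is also one part of a secondary objective, with no hypothesis or power attached, and the same rule applies to both arms.

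Part of this stands. Facility-managed losses may be recorded, so a reader who infers a miscarriage rate of exactly zero, or a 100% undercount, goes further than the article allows. The reply does not remove the conflict. The article states a population and a time point in two places, row 7 still speaks of birth outcomes, and under the looser reading the denominator for miscarriage is undefined. This is a contradiction in what is stated, not a detail left to another document, and an analysis plan cannot recover losses that were not collected. Applying one rule in both arms does not make recording equal in both arms.

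Two other inferences go too far:

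- **A sized undercount of the combined proportion.** Assume losses of 3% to 8% and 20% for the other three events among deliveries. Then 0.03 + 0.97 × 0.20 = 22.4% and 0.08 + 0.92 × 0.20 = 26.4%, against 20%, a shortfall of about 11% to 24% (1 − 0.20/0.224 and 1 − 0.20/0.264). All of these inputs are assumed, and the comparison moves the denominator from facility deliveries to all pregnancies. Row 7 may also be a list of separate proportions; the article does not call it a composite.
- **A missed safety signal.** The article sets no safety objective for miscarriage, so this would be conjecture.

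**Conclusion.** The point holds in a limited form. As stated, the population and the time of observation leave miscarriages largely outside both numerator and denominator, and no other listed source is assigned to capture them. A miscarriage proportion by arm, or its contribution to a combined proportion, therefore cannot be interpreted. This is so whether row 7 is one proportion or several.

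The size of the undercount cannot be derived from the article, because the true risk, the share of losses reaching the facility record and the facility-delivery share are all absent. The conclusion rests on one assumption: that delivery is used in its ordinary sense, which does not include miscarriage. Neither the existence nor the direction of a between-arm bias is shown; the article only gives grounds for not ruling it out.

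The consequence is confined to secondary objective 3. The IPTp3+ primary endpoint, its sample size, and the ANC and SMC coverage outcomes are not affected. The change should be made, but it is not critical to the trial's main conclusion.

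**What to change.** Reconcile secondary objective 3, the Clinical outcomes paragraph and Table 2, row 7:

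1. Limit the delivery-based outcome to stillbirth, low birth weight and preterm birth, over facility deliveries.
2. Either drop miscarriage, or report facility-recorded miscarriages separately and descriptively by arm, naming the register or registers used.
3. State that losses not seen at a facility are missed and that no between-arm conclusion on miscarriage is drawn.
4. If women registered at ANC are used as a denominator, state that registration happens after randomisation and may differ by arm, because the intervention is expected to raise ANC attendance. More or earlier registration in one arm would bring more losses under observation there. The article also does not show that ANC registers can be linked to records of loss, so such a denominator should not be presented as a full remedy.

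The cost is a wording change in the protocol and analysis plan, plus abstraction of facility-recorded losses if that option is taken. The downside is that miscarriage becomes a descriptive, facility-recorded figure only, with no comparison resting on it.
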